## Abstract

Borderline personality disorder (BPD) is a highly disabling psychiatric disorder with emotion dysregulation at its core, resulting in affective instability, impulsivity and sometimes self-harming or suicidal behavior. Sleep is increasingly recognized to play a crucial role in emotion regulation. BPD patients often suffer from (severe) insomnia, potentially aggravating symptoms and preventing recovery from BPD. Yet, the effects of insomnia treatments have not been investigated in context of BPD. Guided internet-based cognitive behavioral therapy for insomnia (iCBT-I; i-Sleep) has been proven effective in improving both insomnia and affective symptoms. In this randomized controlled trial among 96 patients with a DSM-5 diagnosis of BPD (or other personality disorder with ≥4 BPD traits) and insomnia symptoms, we will test the effectiveness of iCBT-I before regular BPD treatment starts, during the waitlist period, on BPD symptoms. Patients in the control group monitor their sleep through a sleep diary during the waitlist period and also receive standard BPD treatment after that. Using linear mixed models we will test the hypothesis that the iCBT-I group improves more than the control group on BPD symptoms (primary outcome), insomnia severity, additional subjective and objective sleep variables, emotion regulation, comorbid anxiety and depression complaints, and quality of life. These effects are thought to arise from a direct effect of improved sleep on emotion regulation and a synergistic effect on the consolidation and internalization of the BPD treatment effect. To our knowledge, this is the first trial assessing effectiveness of CBT-I in patients with BPD (traits). The accessibility of the studied intervention greatly facilitates clinical implication in case of positive results.

## Introduction

1

### Background

1.1

Borderline personality disorder (BPD) is a severe psychiatric disorder with prevalence rates of 1–5 % in the general population, and even 15–28 % in clinical populations (Gunderson et al., 2018). BPD is characterized by an enduring and pervasive pattern of instability in interpersonal relationships, self-image and affects, and marked impulsivity and self-harming and suicidal behaviors (American Psychiatric Association, 2013). Patients with BPD suffer from both emotional dysregulation (e.g., highly reactive mood and emotions, anger attacks, feelings of emptiness, and fear of abandonment), as well as behavioral dysregulation (e.g., impulsive, suicidal, and self-harming behaviors) and cognitive disturbances (identity disturbances, paranoid ideation, and dissociation) (Leichsenring et al., 2011). Given the associated functional impairment and extensive use of (mental) health care, BPD is associated with considerable personal and societal burden, constituting an important public health problem (Juurlink et al., 2018; Juurlink et al., 2020).

Emotion dysregulation lies at the core of all BPD symptomatology (Gunderson et al., 2018). A growing literature highlights the essential role of sleep in emotion regulation and emotional memory processing (Goldstein and Walker, 2014; Rasch and Born, 2013; van der Helm and Walker, 2011). Healthy emotion regulation is thought to depend critically on solid, undisturbed sleep. In contrast, recent studies have indicated that people with insomnia may suffer from fragmented rapid eye movement (REM)-sleep (frequent transitions from REM-sleep to wake and light sleep), which related to a failure of overnight alleviation of emotional distress and amygdala reactivity (Wassing et al., 2019a; Wassing et al., 2019b). Furthermore, sleep is crucial for memory processing (Goldstein and Walker, 2014; Rasch and Born, 2013). During a process referred to as memory consolidation, newly acquired or updated memories are integrated in existing cortical memory networks, stabilizing them and warranting their long-term retention (Dudai et al., 2015; Frankland and Bontempi, 2005). The consolidation of emotional memories is thought to depend primarily on (intact) REM-sleep (van der Helm and Walker, 2011; Nishida et al., 2009). Adequate sleep may therefore be considered imperative for successful psychological treatment, since adjusted dysfunctional memories and newly acquired behavioral and cognitive skills need to be consolidated for psychiatric symptoms to subside (Lane et al., 2015).

Disturbed sleep is thus a highly important factor in BPD severity and recovery. BPD patients often experience severe sleep disturbances (DeShong and Tucker, 2019; Schredl et al., 2012; Vanek et al., 2021). A recent meta-analytic review showed both subjective (e.g. lower sleep quality) and objective (e.g. difficulty falling asleep, reduced sleep efficiency, less deep sleep and higher REM-density) sleep disturbances in BPD (Winsper et al., 2017). Some of these disturbances aggravate emotion dysregulation and self-harming and suicidal behavior in BPD (DeShong and Tucker, 2019; Winsper et al., 2017). Insomnia is the most common of all sleep disorders, characterized by difficulties with initiating sleep, maintaining sleep during the night, and/or waking too early from sleep (American Psychiatric Association, 2013). Up to 63 % of BPD patients report having at least one insomnia symptom nearly every night (Selby, 2013), making insomnia a highly prevalent complaint in BPD.

Until recently, insomnia was most often seen as a consequence or symptom of other psychiatric disorders. Yet, insomnia is increasingly considered a causal factor in development and maintenance of affective psychiatric disorders, because of the centrality of sleep in emotion regulation and emotional memory processing. However, studies assessing the relation between BPD and sleep are scarce. Controlled studies focusing on the role of sleep in BPD treatment are nonexistent (Winsper et al., 2017; Hafizi, 2013). Although effectiveness of sleep therapy in BPD populations is not yet assessed, there is solid meta-analytic evidence that cognitive behavioral therapy for insomnia (CBT-I) is effective also in people with psychiatric disorders, such as depression and post-traumatic stress disorder (PTSD) (Geiger-Brown et al., 2015; van Straten et al., 2018; Wu et al., 2015; Ho et al., 2016). CBT-I commonly consists of three elements: (1) information (psychoeducation, sleep hygiene), (2) behavioral exercises (stimulus control, sleep restriction, relaxation), and (3) cognitive exercises (tackling dysfunctional thoughts about sleep) (Riemann et al., 2017). In order to increase availability and accessibility of CBT-I, guided and unguided internet-based versions have been developed: iCBT-I. A recent meta-analysis showed the effectiveness of iCBT-I for insomnia (Zachariae et al., 2016). Within our group we developed the guided online iCBT-I intervention called i-Sleep. This intervention was tested in four RCT's covering different populations with insomnia complaints, showing large effect sizes on self-reported quality of sleep, sleep-diary derived sleep continuity and secondary outcomes such as symptoms of depression (van Straten et al., 2013; van der Zweerde et al., 2020; van der Zweerde et al., 2018; Leerssen et al., 2021). Adding CBT-I to standard treatment in patients suffering from BPD and insomnia complaints may be promising, not only to reduce sleep disturbances, but also to mitigate BPD symptoms. Yet, the effectiveness of CBT-I has not yet been tested in BPD patients.

### Objectives

1.2

This randomized controlled trial (RCT) investigates the effectiveness of adding guided iCBT-I to standard BPD treatment focusing on emotion dysregulation in patients with BPD or another personality disorder (PD) with ≥4 BPD traits (at least one typical emotional dysregulation symptom) and insomnia complaints before their regular BPD treatment takes place. During the same period, patients in the control group will monitor their sleep in sleep diaries before their regular BPD treatment takes place. We hypothesize that patients who receive guided iCBT-I prior to BPD treatment will improve more than the control group on BPD symptoms (primary outcome), insomnia severity, subjective and objective sleep disturbances (as measured with sleep diary and EEG headband), emotion regulation, comorbid anxiety and depression symptoms, quality of life and daytime functioning (secondary outcomes). We expect that BPD symptoms will improve directly following iCBT-I (a direct effect of improved sleep on emotion regulation) and even further after standard BPD treatment (a synergistic effect of improved sleep on the consolidation and internalization of the treatment effect).

## Methods

2

### Study design

2.1

We will perform a two-armed RCT. In the experimental arm, patients will receive guided iCBT-I for 5–8 weeks followed by a standard BPD treatment (Systems Training for Emotional Predictability and Problem Solving, STEPPS) (Blum et al., 2008). In the control arm, patients are on the waitlist and keep a sleep diary for 6 weeks, followed by STEPPS. The outcomes will be assessed by clinical interviews, questionnaires, sleep diary and EEG headband at baseline (T0), after iCBT-I/waitlist (T1 at 2 months), and after STEPPS (T2 at 8 months). The study design was approved by the Medical Ethics Committee of the VU Medical Centre (METC VUmc; NL76232.029.20). The trial is registered with the Netherlands Trial Register (NL9776).

### Study population

2.2

The study population consists of patients with a DSM-5 diagnosis of BPD or other PD with ≥4 BPD traits, recruited from outpatient departments for personality disorders at specialized mental health care center GGZ inGeest in the Netherlands. All participating patients are registered with the mental health care center and assigned to a psychologist or psychiatrist. In case of crisis or requests for assistance unrelated to sleep, patients are referred to their assigned therapist. All patients with BPD (traits) on the STEPPS-waitlist are potentially eligible participants. For inclusion patients should meet the following criteria: (1) BPD diagnosis, or other PD diagnosis with ≥4 BPD traits (at least one typical emotion dysregulation trait: affective instability, impulsivity, parasuicidal behavior, or anger attacks) according to DSM-5 criteria, as assessed with the Structured Clinical Interview for DSM-5 Personality Disorders (SCID-5-P) (First et al., 2017), (2) 18–65 years, (3) sleep complaints (a score of ≥10 on the Insomnia Severity Index (ISI) (Bastien et al., 2001)), (4) self-considered capability of completing online questionnaires and diaries in Dutch. Exclusion criteria are mostly based on the probable inability to comply with iCBT-I instructions: (1) current diagnosis of bipolar or psychotic disorder, as assessed with a self-report yes/no question, (2) alcohol or drug dependency (a score of ≥20 on the Alcohol Use Disorders Identification Test (AUDIT) (Saunders et al., 1993) or ≥25 on the Drug Use Disorder Identification Test (DUDIT) (Berman et al., 2005)), and (3) having received CBTI in the past 3 months. Using sleep medication is allowed. Patients with sleep disorders other than insomnia (e.g., sleep apnea, narcolepsy) are allowed to participate to enhance generalizability of our results.

### Interventions

2.3

#### iCBT-I

2.3.1

The guided, internet-delivered CBT-I intervention i-Sleep was developed and later updated by VU Amsterdam (van Straten et al., 2013; van der Zweerde et al., 2016). It consists of five sessions: (1) Psycho-education on sleep, disordered sleep and sleep hygiene (i.e. guidelines about health and environmental factors influencing sleep), (2) stimulus control training (i.e. use the bed for sleep only to reinforce association of bed with sleeping) and sleep restriction therapy (i.e. restrict time in bed to average time slept), (3) relaxation techniques and minimizing worrying, (4) tackling dysfunctional cognitions about sleep, and (5) summary and relapse prevention plan (van der Zweerde et al., 2020). See Supplementary material for a more detailed description of the intervention. Patients fill out a sleep diary during the entire treatment period. The treatment takes 5–8 weeks to complete, and is offered online using text and videos. I-Sleep includes experience-based case vignettes of patients. We use an adapted mental health care version of i-Sleep in which case vignettes represent patients with comorbid psychiatric symptoms. Reading the session text and carrying out the homework exercises of i-Sleep take approximately 10–30 min daily. After every session the therapist provides online feedback, guides sleep restriction therapy and bedtimes, and motivates patients to persevere in treatment. Patients can also send questions to their therapist. In general, guidance takes about 20 min per patient per session. There are three additional 30-minute video call appointments (at the start, and after 2 and 4 weeks) to provide extra explanation, enhance commitment, and prevent drop-out. In this study the main researcher will provide the feedback ([name]). She is trained by a psychologist with extensive experience in CBT-I and i-Sleep ([name]) and under weekly supervision by [name] and another experienced CBT(-I) psychologist. I-Sleep will be delivered through the secure web-based platform the Nederlands Slaap Register (www.slaapregister.nl).

#### STEPPS

2.3.2

STEPPS is a 20-week manual-based group treatment for patients with BPD symptoms (Blum et al., 2008). STEPPS is a cognitive-behavioral skills training approach characterizing BPD as a disorder of emotion and behavior regulation. STEPPS aims to improve emotion regulation by becoming more aware of thought patterns, feelings, and behaviors that define BPD, and to acquire emotion and behavior management skills. Patients receive individual treatment parallel to group treatment, mostly to guide homework exercises and provide personal guidance. STEPPS is delivered by trained clinicians working at GGZ InGeest. At some locations of the trial a shortened 10-week version of STEPPS is offered, which is a practice-based adaptation of the 20-week version, including the same goals and core features (Freije, 2016). STEPPS is tested in several RCTs showing moderate to large effects sizes on BPD symptoms (Blum et al., 2008; Bos et al., 2010).

### Study procedure

2.4

A flowchart of the study procedure is displayed in Fig. 1. Fig. 2 shows an additional overview of all assessments and interventions. Patients are recruited through their treating physicians at GGZ InGeest. Patients on the STEPPS-waitlist that provided consent are contacted by the researchers by phone. The researchers then provide information and send the participant information folder and informed consent (IC) by email. If interested in participation, an appointment is scheduled for screening and administering the SCID-5-P, a 119-item semi-structured interview for diagnosing PDs according to DSM-5 criteria (First et al., 2017), to confirm BPD diagnosis and traits. Based on the SCID-5-P screener, other sections may be administered to diagnose possible comorbid PDs. In case the SCID-5-P interview is completed already within the last 6 months before inclusion, these data can be copied from the patient's medical file. Possible comorbid psychiatric disorders are assessed with the Mini-International Neuropsychiatric Interview (MINI) (Sheehan et al., 1998). If eligible, patients are invited to ask questions and sign IC.

**Fig. 1 f0005:**
[figure not shown]
Flowchart of study procedures. Note. BPD: borderline personality disorder; BPDSI: Borderline Personality Disorder Severity Index; iCBT-I: internet-based cognitive behavioral therapy for insomnia; SCID-5-P: Structured Clinical Interview for DSM-5 Personality Disorders; STEPPS: Systems Training for Emotional Predictability and Problem Solving.

**Fig. 2 f0010:**
[figure not shown]
Schedule of enrolment, interventions, and assessments. Note. T1 and T2 are 2 months and 8 months after baseline respectively. Use of medication and treatment is additionally assessed between T1 and T2; at 4 months and 6 months.

Subsequently, patients commence with the T0 assessment, which contains all outcome measures and an online baseline survey. All outcome assessments are repeated at T1 (2 months after T0, after either iCBT-I and ideally before STEPPS starts, or waitlist) and T2 (8 months after T0, after STEPPS). Use of psychotropic medication and psychotherapeutic treatment is additionally assessed at 4 and 6 months after T0. After T0, patients are randomly assigned to iCBT-I group or the sleep diary-keeping control group. During all phases of the trial, there is one central contact person to provide support to all patients. After completion of the trial, patients in the control condition will be offered identical treatment of remaining sleep problems.

Patients may withdraw from participation at any time, for any reason, without consequences for their awaited treatment. We aim to perform intention-to-treat analyses, so patients that decide to withdraw from treatment are asked to continue the outcome assessments. We will continue recruitment until the intended sample size is achieved or until funding restrictions compel us to end assessments. Data of patients that withdraw from participating are used and reported, unless patients ask us to destroy any data.

### Outcomes and measurements

2.5

#### Primary outcome measure

2.5.1

The primary outcome is BPD severity, as assessed with the BPDSI-5-4wk. This clinician-rated, semi-structured interview is administered at T0, T1, and T2. The BPDSI-5-4wk is an adjusted version of the BPDSI-5 and measures BPD symptom severity over a period of the past 4 weeks instead of 3 months (Arntz and Wibbelink, 2019). The BPDSI-5-4wk is based on the DSM-5 criteria for BPD and consists of 70 items assessing behaviors and cognitions related to abandonment, relationships, self-image, impulsivity, (para)suicidal behavior, mood swings, feelings of emptiness, anger attacks, and dissociation and paranoid ideation on an 8-point scale ranging from 0 to 10. Scoring options of the BPDSI-5 are adjusted for the BPDSI-5-4wk to (0) never/4 weeks, (3) once/4 weeks, (5) twice/4 weeks, (6) three times/4 weeks, (7) once a week, (8) multiple times a week, but less than half of the week, (9) more than half of the week, and (10) daily. Note that scores 1, 2, and 4 have been omitted, to obtain the same frequency to time ratio used in the BPDSI-5. The BPDSI has high interrater reliability, acceptable to high internal consistencies, and very good discriminant and concurrent validity (Giesen-Bloo et al., 2010).

#### Secondary outcome measures

2.5.2

##### Self-reported BPD severity

2.5.2.1

BPD severity is additionally assessed using a self-report questionnaire, the BPD Checklist – ultra-short (ultra-short BPD-C) (Bloo et al., 2017; Wibbelink and Arntz, 2020). This additional measure allows us to combine data with parallel studies assessing the effectiveness of iCBT-I in other psychiatric populations. The ultra-short BPD-C consists of nine items rated on a scale of 1 (not at all) to 5 (very much), one for each DSM-5 BPD diagnostic criterion, with higher sum scores indicating higher BPD severity. The ultra-short BPD-C has good internal consistency, and good convergent, discriminant, and construct validity (Wibbelink and Arntz, 2020).

##### Insomnia severity

2.5.2.2

Insomnia severity is measured with the ISI (Bastien et al., 2001). The ISI has seven items rated on a scale of 0 to 4, with higher sum scores indicating more severe insomnia. The ISI has adequate internal consistency, is sensitive to change, and has been validated for online use (Thorndike et al., 2011; Morin et al., 2011).

##### Subjective sleep (sleep diary)

2.5.2.3

Patients keep a sleep diary that is based on the Consensus Sleep Diary (CSD) (Carney et al., 2012) for 1 week to establish the following sleep parameters: sleep onset latency, sleep efficiency, number of awakenings, wake after sleep onset, terminal wakefulness, total sleep time, and subjective sleep quality. Patients also rate how energized, depressed, anxious, and distressed they feel on a scale of 0 (not at all) to 4 (very much) each morning and optionally also in the evening. Patients are asked to fill out the sleep diary every morning, preferably 30–60 min after awakening. Note that sleep diary data that is collected between T0 and T1 as part of either iCBT-I or the sleep diary control condition will not be used as outcome measure.

##### Objective sleep (EEG headband measurements)

2.5.2.4

To measure sleep objectively, patients are asked to sleep with an EEG headband (ZMax, Hypnodyne) for four nights at each assessment. The ambulatory EEG headband, which is easy to use and comfortable, is send to the patient's home with clear instructions for use. Sleep parameters that are derived from EEG measurements concern sleep continuity measures (e.g. sleep efficiency and number of awakenings) as well as sleep architecture measures (e.g. duration and percentage of the different sleep stages and REM-fragmentation). EEG assessments are optional and patients are not excluded if they are unwilling to sleep with the headband.

##### Emotion regulation

2.5.2.5

Emotion regulation is measured with the Difficulties in Emotion Regulation Scale – Short Form (DERS-SF) (Kaufman et al., 2016). The DERS-SF consists of 18 items, rated on a scale from 1 (almost never) to 5 (almost always), loading onto six subscales: (1) lack of emotional awareness, (2) lack of emotional clarity, (3) difficulty regulating impulsive behavior, (4) difficulty engaging in goal-directed behaviors, (5) non-acceptance of emotional responses, and (6) lack of access to emotion regulation strategies. Total scores range from 18 to 90 with higher scores indicating more difficulties in emotion regulation. The DERS-SF has good internal consistency and construct validity (Hallion et al., 2018; Skutch et al., 2019). However, because the psychometric soundness of the DERS-SF subscale covering emotional awareness is lacking (Hallion et al., 2018; Moreira et al., 2020), these questions are replaced by questions of the DERS-18 (Victor and Klonsky, 2016), in line with the procedure in Wibbelink et al. (2022).

##### Severity of anxiety and depression symptoms

2.5.2.6

Symptoms of generalized anxiety disorder (GAD), social anxiety disorder (SAD), panic disorder (PD), PTSD and major depressive disorder (MDD) are assessed using the Rapid Measurement Toolkit-20 (RMT-20) (Batterham et al., 2020). The RMT-20 is a self-report questionnaire with five times four items, rated on a scale of 1 (never) to 5 (always), assessing the severity of each disorder. Higher scores indicate higher anxiety or depression severity. The RMT-20 has high internal consistency and excellent sensitivity and specificity (Batterham et al., 2020).

##### Additional outcomes

2.5.2.7

Additional outcome measures consist of quality of life, daytime functioning, positive mental health, and life satisfaction outcomes (see Supplementary material for description).

#### Baseline measurements

2.5.3

Several baseline measurements are obtained through online survey and used for covariate-adaptive randomization, population description and effect modification analyses. Demographic data include sex, age, nationality, height and weight, employment, and education. Questions regarding use of psychotropic medication and psychotherapeutic treatment are repeated every 2 months until T2. Additionally, sleep quality, chronotype, and symptoms of sleep disorders other than insomnia are assessed at baseline (see Supplementary material).

#### Adverse effects

2.5.4

Potential adverse effects are assessed in two ways, in line with procedures in van der Zweerde et al. (2016). First by assessment of BPD and insomnia severity. Exacerbation of BPD or insomnia severity from pre- to post-iCBT-I may indicate adverse effects. Second, patients report at T1 and T2 whether they experienced (1) falling accidents, (2) traffic accidents, and (3) any other negative events they think are related to sleepiness or fatigue.

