## Discussion

3

Severe emotion dysregulation lies at the core of BPD, resulting in typical symptoms such as affect instability, fear of abandonment and impulsive or self-harming behavior. Healthy emotion regulation depends critically on solid, undisturbed sleep, yet sleep disturbances such as insomnia are extremely common in BPD. By improving sleep through guided iCBT-I prior to emotion regulation treatment, we aim to improve sleep as well as mitigate BPD symptoms. Better sleep may promote more efficient processing and overnight alleviation of (negative) emotions accumulated during the day, as well as affective stability the next day. On a symptom level this may result in fewer mood swings, inappropriate anger attacks, intense feelings of emptiness and fears of abandonment. Emotional dysregulation also drives the severe behavioral and cognitive symptoms in BPD. We therefore expect better sleep to similarly result in less self-damaging or suicidal behavior, impulsiveness and paranoid ideation. Apart from these direct effects, we expect that optimizing sleep with iCBT-I prior to standard BPD treatment will also facilitate (memory) consolidation of the treatment outcome. Newly acquired emotion regulation skills and adjusted dysfunctional beliefs about self and others will be more strongly internalized, further reducing BPD symptom severity. For secondary outcomes we expect an improvement in insomnia complaints, subjective and objective sleep disturbances (sleep diary and EEG headband), emotion regulation, anxiety and depressive symptoms, and quality of life and daytime functioning. Our ultimate goal is to test the efficacy of iCBT-I as add-on therapy for BPD with comorbid sleep complaints and include the intervention in clinical guidelines of BPD in case of positive results. Findings may similarly spark new investigations into effectiveness of iCBT-I for other psychiatric disorders deriving from emotion dysregulation and/or maladaptive memory processing along with sleep problems.

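### Cheap improvement, not an error: neither adverse-effect route in section 2.5.4 isolates self-harm, and a descriptive summary of (para)suicidal items already collected would do so

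*Protocol article*

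**What the plan says.** Section 2.5.4 (Adverse effects) states two routes, following the procedure of an earlier i-Sleep publication.

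- **Symptom route:** "First by assessment of BPD and insomnia severity. Exacerbation of BPD or insomnia severity from pre- to post-iCBT-I may indicate adverse effects". No instrument, domain or threshold is named.
- **Event route:** at T1 and T2 patients report falls, traffic accidents and "any other negative events they think are related to sleepiness or fatigue".

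The trial has two measures of BPD severity. The primary outcome, the BPDSI-5-4wk (section 2.5.1), "consists of 70 items assessing behaviors and cognitions related to abandonment, relationships, self-image, impulsivity, (para)suicidal behavior, mood swings" and three further areas: emptiness, anger attacks, and dissociation with paranoid ideation. That makes nine. "This clinician-rated, semi-structured interview is administered at T0, T1, and T2", and section 2.6 says the rater is blinded. The second measure, the ultra-short BPD-C (section 2.5.2.1), has nine items, "one for each DSM-5 BPD diagnostic criterion, with higher sum scores indicating higher BPD severity".

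On why self-harm matters here, section 1.1 says of sleep disturbances: "Some of these disturbances aggravate emotion dysregulation and self-harming and suicidal behavior in BPD". Section 3.1 accepts that sleep restriction may temporarily raise emotional symptoms. The Discussion expects benefit in this domain: "We therefore expect better sleep to similarly result in less self-damaging or suicidal behavior, impulsiveness and paranoid ideation".

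**The concern.** In a first trial of CBT-I in patients with BPD traits, with sleep restriction as a component, self-harm is the harm a reader will look for. The protocol's own rationale links it to sleep. Yet the two routes reach it only indirectly. The symptom route uses BPD severity, which treatment is expected to lower, and insomnia severity, which does not measure self-harm. The event route picks up self-harm only when the patient attributes it to sleepiness or fatigue.

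If the symptom route is read at the level of a whole score, a small or moderate rise in self-harm can be diluted by stable parts or offset by improving ones. What is at stake is the clarity of the harm report. The efficacy result is not in question.

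**Working it through.** **1. The plan's own figure.** Section 2.7 gives d = 0.5, α = 0.05 (two-sided assumed), power 0.80, a correlation of 0.5 among repeated measures, and an effect averaged over T1 and T2. The variance factor for the mean of two measures is (1 + 0.5)/2 = 0.75. Then n = 2 × ((1.960 + 0.842)/0.5)² × 0.75 = 62.79 × 0.75 = 47.09, rounded up to 48 per arm. This reproduces. It serves below only as the denominator; nothing proposed here changes it.

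**2. Which route reaches self-harm?**

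| Signal in 2.5.4 | Reaches self-harm? |
|---|---|
| BPD severity | As one of nine parts |
| Insomnia severity | Not directly; it could rise if harm runs through worse sleep |
| Falls, traffic accidents | No |
| Other events | Only if the patient links them to sleepiness or fatigue |

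**3. Dilution in a nine-part score.** The BPD-C is fully specified in section 2.5.2.1.

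- Range: 9 × 1 = 9 to 9 × 5 = 45, a span of 36 points.
- Largest possible rise in the self-harm item: 5 − 1 = 4 points, and 4/36 = 11% of the span.
- A one-point fall on four of the other eight items cancels that rise.

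The article gives no scoring formula for the BPDSI-5-4wk, so no such figure is given for it. The principle that a rise in one part can be offset by falls in the others applies to any score that adds its parts. How often this would happen cannot be derived from the article. It would need correlations between domains and domain-level effects, and neither is stated.

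**4. What the proposed table could show.** The counts of newly positive patients are assumed, with 48 per arm. The Wilson limits for a proportion p are [p + z²/2n ± z√(p(1−p)/n + z²/4n²)] / (1 + z²/n). Newcombe's interval for the difference D = p₁ − p₂ runs from D − √((p₁−l₁)² + (u₂−p₂)²) to D + √((u₁−p₁)² + (p₂−l₂)²).

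Example, 5 vs 5: p = 10.42%, Wilson limits 4.53% to 22.17%, half-width √(5.89² + 11.75²) = 13.1 points.

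| iCBT-I vs control, of 48 | Difference (points) | 95% interval |
|---|---|---|
| 5 vs 5 | 0 | −13.1 to +13.1 |
| 10 vs 5 | +10.4 | −4.4 to +25.1 |
| 14 vs 5 | +18.8 | +2.7 to +33.9 |
| 14 vs 14 | 0 | −17.8 to +17.8 |

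The table can describe a rise but cannot exclude one.

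**5. Recall window.** The instrument covers four weeks (section 2.5.1) and T1 is at two months (section 2.1), so the T1 window opens roughly in week 5. Sleep restriction starts in session 2 of five (section 2.3.1). If the course starts soon after T0 and its sessions are evenly spaced over 5 to 8 weeks (both assumed), session 2 begins in week 2. Self-harm in the first weeks of restriction can therefore fall outside the window.

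**The case against.** The strongest reply is that nothing here is wrong. Section 2.5.4 does not say total score, sets no rule and does not rule out looking at domains. An item-level table is the kind of detail an article may leave to the full protocol or analysis plan. That stands, and it is why the point is an improvement and not a correction.

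Second, the pathways the protocol describes work against masking. Section 1.1 has disturbed sleep aggravating emotion dysregulation and self-harm together, section 3.1 speaks of emotional symptoms in general, and the Discussion expects the domains to improve together. Insomnia severity, already a signal, could also rise if the harm ran through worse sleep. No passage describes self-harm rising alone, and a large rise would usually still show in an overall score. This also stands. It limits how likely masking is, but it does not make the existing routes specific to self-harm.

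Third, the remedy is imprecise and its recall window is short. Both are true, as steps 4 and 5 show. A descriptive count by arm is still more informative about self-harm than a score in which it is one of nine parts.

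A reader might go further and infer that self-harm is unmonitored. The documents do not support this. Section 2.2 refers patients in crisis to their assigned therapist, and serious-event reporting may sit in the full protocol, which is not shown.

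**Conclusion.** The point holds as an optional improvement. Section 2.5.4 names two ways of assessing adverse effects, and neither isolates self-harm. BPD severity serves as both harm signal and efficacy construct, with self-harm one of nine areas; on the BPD-C that part can move the sum by at most 4 of 36 points. The protocol's rationale gives a reason to report this harm separately.

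The dilution argument rests on reading BPD severity as an overall score. Sections 2.5.1 and 2.5.2.1 suggest that reading, but 2.5.4 does not state it. A reader might also infer that masking is probable or can be quantified; the article gives no inputs for that, so no frequency is claimed. Sample size, error rate and primary inference are untouched.

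**What to change.** Keep both existing routes and add to section 2.5.4:

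*Self-harm and suicidal behavior are also summarised as a descriptive harm outcome, using the (para)suicidal items of the BPDSI-5-4wk. For each arm at T1 and T2 we report the number of patients with a higher score than at T0 and the number newly positive (0 at T0, above 0 at follow-up), with the between-arm difference and its 95% confidence interval and no significance test.*

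The cost is two sentences and one table. The items are already collected by a blinded rater in both arms at T0, T1 and T2, so no visit, staff time or patient is added. When reporting, state the two limits: the wide intervals, and the four-week recall that may leave early sleep restriction uncovered at T1. Naming the summary in advance also avoids choosing a domain after the results are seen.
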